**2. RESEARCH PLAN**

**2.1 Introduction**

Disorders of serum sodium are the most common electrolyte disorder in hospital practice [1] and represent a significant healthcare burden [2]. Mild hyponatremia (i.e. plasma sodium 130-135mmol/l) is found in as many as 15-30% of hospitalized patients [3-6]. More severe hyponatremia (plasma sodium <130mmol/l) is seen in 1-4 % of inpatients [7]. Hyponatremia in hospitalized patients has a significant mortality ranging from 5% to 50%, depending on severity and acuity of onset as well as comorbidities. Hypernatremia is far less common but mortality ranges from 60 to 75% [8].

The central nervous system (CNS) plays an integral role in the neuroendocrine regulation of sodium and water homeostasis. Hyponatremia is the most common electrolyte disorder encountered in the neurologic intensive care unit [3,9,10]. It is seen in patients with subarachnoidal hemorrhage (SAH) [11], brain tumors [12-14] and ischemic stroke [15-17], complicating their clinical courses [9]. A timely and accurate diagnosis followed by a correct treatment is crucial [18,19]. Differential diagnoses include the syndrome of inappropriate antidiuretic hormone secretion (SIADH), cerebral salt wasting (CSW), hypo- or hypervolemic hyponatremia, and mixed cases [20]. Besides measurement of plasma osmolality and sodium concentration in urine, determination of the extracellular fluid volume remains the most important discriminatory element. However, its prediction based on clinical signs and routine laboratory evaluation has a limited sensitivity and specificity of <50% [21,22]. Accordingly, only 10% of physicians reach the correct diagnosis of the underlying cause of hyponatremia with the routinely used clinical diagnostic algorithms [23]. Thus, there is demand for more reliable parameters to improve the diagnosis of sodium imbalance in patients with CNS disease.

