**2.2 DETAILED RESEARCH PLAN**

**A. Objectives**

The objectives of this trial are to evaluate

1. The diagnostic value of copeptin levels in the diagnosis of water imbalance in patients with stroke and patients undergoing intracranial surgery.
2. The prognostic accuracy of copeptin levels and other biomarkers to predict the clinical outcome in patients with stroke and patients undergoing intracranial surgery.

Specific objectives of the study are:

- - 1. **Diagnostic Study:**

**Hyponatremia** will be defined as serum sodium concentration below 135 mmol/L [31].

Specifically, we aim to investigate whether Copeptin levels can facilitate the differential diagnosis of hyponatraemia. Thereby, we will use a standardized clinical algorithm based on medical history, drug history, clinical assessment of the extracellular fluid volume, and laboratory parameters such as plasma and urine sodium concentration, plasma and urine osmolality, creatinine, uric acid, urea, total protein, albumin, TSH, fT4, T3, blood glucose, urea nitrogen, plasma potassium to evaluate the aetiology of hyponatraemia (**figure 1**). In our cohort, wee expect a prevalence of around 20 % (i.e. around 75 patients of the 350 patients derived from the power calculation, see below) to have hyponatraemia. The etiologies are listed in Figure 1 including the estimated relative contributions and the most frequent diagnosis within the subgroup is underlined.

**Figure 1** Diagnostic algorithm of hypotonic hyponatraemia:

We **hypothesize** that overall, included patients will have moderately but significantly higher copeptin levels (around 5pmol/L) as compared to healthy controls (4pmol/L). In patients with hyponatraemia, copeptin levels will be lower as compared to patients without hyponatraemia, however, with a wide range (1.7pmol/L (detection limit) to 15pmol/L). Analysing the subgroup of patients with hyponatraemia, we assume that in patients with SIADH, copeptin levels will be markedly increased (i.e. 12pmol/L), moderately increased (8pmol/L) in hypovolemic hyponatraemia and suppressed in hypervolemic hyponatraemia (<2pmol/L). Importantly, we anticipate to identify SIADH as a co-factor also in some patients with “typical” hypervolaemic and hypovolemic hyponatremia, where ADH disturbances have been neglected previously due to the incapability to assess circulating ADH levels.

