**Hypernatremia**

Hypernatremia will be defined as a rise in the serum sodium concentration to a value exceeding 145 mmol/L [3]. Again, we will use a standardized clinical algorithm based on clinical and laboratory parameters to evaluate the aetiology of hypernatraemia.

Of all 350 patients included (see sample size considerations) we expect 10 % (i.e. around 45 patients) to have hypernatraemia. The etiologies are listed in Figure 1 including the estimated relative contributions and the most frequent diagnosis within the subgroup underlined in red..

**Figure 2** Diagnostic algorithm of hypernatraemia

We **hypothesize** that in patients with hypernatraemia, copeptin levels overall will be higher as compared to patients without hyponatraemia, however, with a wide range (1.7pmol/L (detection limit) to 12pmol/L). Analysing the subgroup of patients with hypernatraemia, we assume that in patients with Diabetes insipidus, copeptin levels will be markedly decreased (i.e. 1.7-2pmol/L), moderately increased (8pmol/L) in hypervolemic hyponatraemia and markedly increased in hypervolemic hyponatraemia (12pmol/L).

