**Statistical Analyses**

Copeptin levels will be assessed in a blinded batch analysis upon completion of the plasma asseveration.

Discrete variables will be expressed as counts (percentage) and continuous variables as means ± standard deviation (SD) or median (interquartile range), unless stated otherwise. First, the overall prevalence of hyponatraemia in neurological and neurosurgical patients will be assessed. Frequency comparison will be done by chi-square test. Two-group comparison of normally distributed data will be performed by Students t-test. For multigroup comparisons, one-way analysis of variance with least square difference for posthoc comparison will be applied. For data not normally distributed, the Mann-Whitney-U test is used if only two groups are compared. The Kruskal-Wallis one-way analysis of variance with Bonferroni’s multiple posthoc test will be used if more than two groups were being compared.

Furthermore we will do a correlation analysis of copeptin levels with sodium levels, serum osmolality and other diagnostic laboratory parameters. Correlation analyses will be performed by using Spearman rank correlation. Levels that are non-detectable will be assigned a value equal to the lower limit of detection for the assay. All testing will be two-tailed and P values less than 0.05 were considered to indicate statistical significance. Scatterplot data will be shown with GraphPad Prism®, Version 4.00 for Windows (GraphPad Software, San Diego California, USA).

We will then compare the diagnostic accuracy of Copeptin levels with other potential biomarkers for sodium imbalance, e.g. atrial natriuretic peptide (ANP) and B-type natriuretic peptide (BNP). The ability of Copeptin to foresee sodium disbalance before it becomes evident by laboratory analysis will be assessed. Therefore we will correlate Copeptin levels with sodium level changes over time.We will construct receiver operating characteristic (ROC) curves and determine the areas under the receiver operating characteristic curve (AUC). The sensitivity and specificity to predict the correct diagnosis of hyponatraemia will be determined, based on the above standardized algorithm [32]. This ascertainment will be done retrospectively on the basis of the review of the complete patient charts by two study investigators, blinded to each other’s diagnosis. Discordant cases will be mutually discussed and resolved. Patients will be managed as usual according to the state of the art treatment.

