**Statistical Analyses**

Basic statistical analyses will be performed as described in the diagnostic study. We will evaluate 18 known predictors (i.e. *age; sex; clinical features* (NIHSS or GCS), *important comorbidities* (coronary artery disease, heart failure, atrial fibrillation, hypertension on admission, previous TIA/Stroke, renal disease, dementia, diabetes); *location of the lesion* (LACS etc.); *stroke subtype by the TOAST criteria*; *therapies* (thrombolysis); *laboratory parameters (*baseline glucose level on admission [46-50], CRP); *body temperature*; *smoking histo*ry), and copeptin levels in our multivariate analysis. All variables will first be tested one by one against the dependent variable unfavorable outcome (defined either as Barthel index <85 or modified Ranking scale 3 to 6) for the presence of a significant association. Only variables significantly associated with the outcome will be assessed in a multivariate model performed separately for each parameter.

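### Copeptin enters the prognostic model only if significant in a one-variable test, and the tests named could miss a two-ended relation that the protocol's own expected values make plausible

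*Protocol*

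**What the plan says.** The Statistical Analyses text of section 2.2.2 (Prognostic Study) lists 18 known predictors "and copeptin levels in our multivariate analysis. All variables will first be tested one by one against the dependent variable unfavorable outcome". The outcome is binary: Barthel index below 85, or modified Rankin 3 to 6. The gate follows: "Only variables significantly associated with the outcome will be assessed in a multivariate model performed separately for each parameter". Section E (Sample Size considerations) repeats it and adds stepwise logistic regression. The list in section E omits copeptin; the list in section 2.2.2 includes it.

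For the one-variable step, section 2.2.2 says "Basic statistical analyses will be performed as described in the diagnostic study". That earlier section names the t-test for normal data, Spearman correlation, and for the rest "For data not normally distributed, the Mann-Whitney-U test is used if only two groups are compared". The threshold is also there: "All testing will be two-tailed and P values less than 0.05 were considered to indicate statistical significance".

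On expected levels, section 2.2 A gives about 5 pmol/L for the cohort. At the low end, copeptin is "suppressed in hypervolemic hyponatraemia (<2pmol/L") and "in patients with Diabetes insipidus, copeptin levels will be markedly decreased (i.e. 1.7-2pmol/L"). At the high end it is 8 pmol/L in hypovolemic hyponatraemia and 12 pmol/L in SIADH. On risk, section 2.1 gives mortality of 5% to 50% for hyponatraemia and adds: "Hypernatremia is far less common but mortality ranges from 60 to 75"%.

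**The concern.** Hypothesis 2 is that copeptin predicts outcome, and section 2.2.2 asks for this whether or not it acts through sodium imbalance. If patients with sodium disorders do worse, and those disorders sit on both sides of the usual copeptin level, then patients with a poor outcome have a wider spread of copeptin but much the same mean and median. A t-test, a rank test or a single logistic slope sees little, because the two ends pull in opposite directions. The gate then removes copeptin, and the study reports no prognostic value without having fitted the adjusted model. None of the 18 predictors is sodium status, so nothing else in the model would carry that part of the risk.

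**Working it through.** **Plan's own figures.** 18 predictors × 10, 15 and 20 observations = 180, 270 and 360, as stated. Expected inclusion: 480 × 0.80 × 0.90 = 345.6, against a stated figure of about 350. The plan gives no power, effect size, outcome rate or SD for copeptin, so there is no power figure to reproduce.

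**Inputs from the protocol.** N = 350; two-sided 0.05; 20% hyponatraemia plus 10% hypernatraemia, so 30% with a sodium disorder; centres of 5 pmol/L (normal sodium), about 1.9 (low end) and 8 or 12 (high end). Values were floored at 1.7, the detection limit given in section 2.2 A.

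**Assumed inputs.** Unfavourable outcome 30% at normal sodium and 50% or 60% at both ends; log-SD 0.3 or 0.6; low-end share of sodium disorders 20% to 80%; a monotone stress slope of 0 to 1.0 log-odds per log unit of copeptin.

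**Is a balanced mix credible?** Figures 1 and 2, which hold the shares by cause, are not shown. Section 2.2 A does expect copeptin to be lower in hyponatraemia than without it. Take the low-end level as 1.8 and let s be the low-end share within hyponatraemia. A mean below 5 needs 1.8s + 8(1 − s) < 5, so s > 3.0/6.2 = 48% if the rest sit at 8, or s > 7.0/10.2 = 69% if they sit at 12. Hyponatraemia is 20/30 of expected sodium disorders. Even if every hypernatraemia were high, the low-end share overall would be at least 0.48 × 2/3 = 32%. Shares of 35% to 65% are therefore in reach.

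**Power without a stress effect** (outcome 30% against 60%, log-SD 0.3, 1,500 runs per row):

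| Low-end share | One slope, raw | One slope, log | Mann-Whitney | Log + log² (2 df) |
|---|---|---|---|---|
| 20% | 70% | 42% | 51% | 90% |
| 35% | 37% | 10% | 13% | 91% |
| 50% | 13% | 9% | 7% | 93% |
| 65% | 8% | 36% | 29% | 96% |
| 80% | 31% | 76% | 72% | 98% |

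At a 50% share the mean AUC is 0.49. With outcome 30% against 50% at that share, power is 9%, 7% and 6%, against 64%. With N = 180 and outcome 30% against 60%, it is 9%, 6% and 6%, against 68%.

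**Variant** (n = 346, log-SD 0.5, odds ratio 2.5 to 4 for a sodium disorder, shares 35% to 65%, no stress effect): raw slope 6-25%, Mann-Whitney 6-35%, 3-knot spline on log copeptin 38-86%.

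**Power with a stress effect** (settings of the table):

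| Slope, low-end share | Raw | Log | Mann-Whitney | Log + log² |
|---|---|---|---|---|
| 0.4, 50% | 71% | 28% | 33% | 96% |
| 0.4, 65% | 35% | 8% | 8% | 92% |
| 0.7, 50% | 96% | 77% | 80% | 99% |
| 0.7, 65% | 80% | 42% | 44% | 95% |
| 1.0, 50% | ≥98% | 98% | 98% | ≥98% |

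With log-SD 0.6, slope 0.7 and a 50% share, the raw slope has 99% and the quadratic 98%. In the n = 346 variant, a stress odds ratio of 1.3 per 0.7 log units gives raw 29-85%, Mann-Whitney 10-72% and spline 48-90%.

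**Cost if the truth is monotone** (n = 346, odds ratio 1.4 per SD of log copeptin, log-SD 0.54 to 1.0): single log slope 0.83-0.85, raw slope 0.67-0.79, spline with joint 2-df test 0.76. The loss against a single log slope is 7 to 9 points. As a check, 1-df power of 0.833 to 0.849 implies a non-centrality of about 8.6 to 9.0, and a 2-df test at that value has power 0.75 to 0.77.

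**The case against.** The protocol never says linear, raw scale or one slope. A reader might infer a single straight-line effect from the phrase about levels, but the functional form is unstated and may be set in an analysis plan that is not shown. That stands. It does not rescue the gate, which the protocol itself states twice, or the named tests, which are all monotone whatever the scale.

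A reader might also infer that the protocol's figures establish raised risk at both ends. They do not. Section 2.1 gives mortality by direction of sodium, not by cause, from 5% upward for hyponatraemia. Nothing is given for Barthel or Rankin outcome in diabetes insipidus or hypervolemic hyponatraemia. Two of the high values in the Hypernatremia text (8 and 12 pmol/L) both carry the label hypervolemic hyponatraemia and need reconciling. Some sodium disorders may also arise after the sample is taken.

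The rationale the protocol does give is monotone: section 2.1 says ADH rises with stroke severity. With a strong effect of that kind every test passes and the flexible term gains nothing. That stands too, but the tables show that a modest stress effect does not reliably save the screen when half or more of the sodium disorders are at the low end.

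Finally, the study is exploratory and a spline is one choice among several. This argues against prescribing a 2-df primary test. It does not argue for letting a p-value decide whether the study's own marker is reported.

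**Conclusion.** The point holds in a limited form and should be acted on. As written, the plan can discard copeptin on a one-variable test that is blind to a two-ended relation, and the protocol's expected levels make such a relation plausible. With no stress effect and low-end shares of 35-65%, power was roughly 6-37% for one-slope or rank tests, against about 38-96% with a flexible term. The gap narrows when one end dominates and largely closes under a strong monotone effect. These figures rest on assumed outcome risks, spread and mix. A false negative for hypothesis 2 is a material risk. The documents do not support the stronger reading that it is the expected result. Nor is a mandatory spline test almost free: the figure of 7 to 9 points makes it a real trade-off.

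**What to change.** In the Statistical Analyses of section 2.2.2 and in section E, exempt copeptin from the significance screen and from stepwise removal, and always report its estimate adjusted for the other predictors. State that copeptin enters on the log scale, with a supporting check for non-linearity (for example a 3-knot restricted cubic spline or a quadratic term) and the fitted curve reported. Fix this before copeptin is read. The blinded batch assay after sample collection allows that, whereas choosing the curve afterwards would be data-driven. Reconcile the two detection limits first (1.7 pmol/L in section 2.2 A, 0.4 in the measurement section), because undetectable values are set to the limit and this shapes the low end on the log scale.

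Cost: the exemption is close to free. The 18 listed predictors do not include copeptin, so it is the 19th, and a non-linear term is the 20th. On the plan's own counting rule that leaves 350/20 = 17.5 observations per term at the expected size, but 180/20 = 9 at the minimum size, just under its floor of 10. The loss of 7 to 9 points arises only if the joint 2-df test is made primary and the effect is monotone on the log scale. Keeping the check supporting avoids it.

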**Study hypothesis:** 1. Copeptin will improve the diagnostic accuracy to diagnose sodium imbalances as compared to routinely used markers 2. Copeptin will be a reliable prognostic tool, dependent or independent of sodium imbalance, to predict short-term (i.e. in-hospital) and medium-term (i.e. 3 months) clinical outcome in stroke patients. Further other biomarkers will be measured to assess prognostic values.

**Analysis:** Our sample size consideration is based on the second prognostic question to predict the outcome of neurological and neurosurgical patients. To determine an optimal clinical model we will undertake a multivariable regression analysis to assess which variables are independently associated with outcome. Multiple regression models with a minimum of 10 to 15 observations per predictor variable reveal good estimates. We will evaluate 18 predictors in our multivariate analysis. Therefore, we aim to include a minimum sample size of 180 patients (for 10 observations per predictor) to 270 (for 15 observations per predictor) and a maximum sample size of 360 patients (for 20 observations per predictor).

**Significance:** Despite the frequent occurrence and the poor outcomes of serious disorders of sodium balance, few controlled data are available to guide the clinician. A better diagnostic approach to determine the etiology of hyponatremia should improve patient management. Copeptin as a prognostic marker in neurological and neurosurgical patients could become an innovative tool to guide early treatment decisions, discharge from the stroke unit and application of interventions.

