**E. Sample Size considerations**

Design

This is a prospective observational study to evaluate Copeptin as a diagnostic and prognostic marker in neurological and neurosurgical patients.

Analysis

Analysis tools

All relevant clinical and laboratory parameters obtained by interview, clinical tests and reviewing of the medical records will be entered into an Excel® database. Statistical Analysis System (SAS® Institute, Cary, NC, USA) and R for Windows (R Foundation for Statistical Computing, www.r-project.org) will be used for data analysis. Statistical evaluation will include stepwise logistic regression analysis to assess which variables are independently associated with outcome.

Sample size considerations

Our sample size consideration is based on our intention to determine an optimal clinical model to predict the outcome of neurological and neurosurgical patients (based on Barthel index, Rankin scale NIHSS scale and Glasgow outcome scale) (i.e. the prognostic question of the study). To determine an optimal clinical model we will undertake a multivariable regression analysis. It has been demonstrated that multiple regression models with a minimum of 10 to 15 observations per predictor variable reveal good estimates [45]. We will evaluate 18 known predictors (i.e. *age; sex; clinical features* (NIHSS or GCS), *important comorbidities* (coronary artery disease, heart failure, atrial fibrillation, hypertension on admission, previous TIA/Stroke, renal disease, dementia, diabetes); *location of the lesion* (LACS etc.); *stroke subtype by the TOAST criteria*; *therapies* (thrombolysis); *laboratory parameters (*baseline glucose level on admission [46-50], CRP); *body temperature*; *smoking histo*ry) in our multivariate analysis. Therefore, we aim to include a minimum sample size of 180 patients (for 10 observations per predictor) to 270 (for 15 observations per predictor) and a maximum sample size of 360 patients (for 20 observations per predictor). All variables will first be tested one by one against the dependent variable unfavorable outcome (defined either as Barthel index <85 or modified Ranking scale 3 to 6) for the presence of a significant association. Only variables significantly associated with the outcome will be assessed in a multivariate model performed separately for each parameter.

Based on the last year’s data in our hospital, the following number of patients with stroke and neurosurgery will be eligible:

*Patients*

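### Univariable screening plus stepwise selection, with no covariate forced in and copeptin itself screened, cannot reliably show that copeptin is independently associated with outcome

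*Protocol*

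**What the plan says.** The Synopsis (Analysis) gives the aim as a "multivariable regression analysis to assess which variables are independently associated with outcome". Section 2.2.2 (Prognostic Study, Statistical Analyses) and section E (Sample Size considerations) set the same two-stage rule. First, "All variables will first be tested one by one against the dependent variable unfavorable outcome"; then, "Only variables significantly associated with the outcome will be assessed in a multivariate model performed separately for each parameter". The Analysis tools paragraph of section E adds: "Statistical evaluation will include stepwise logistic regression analysis to assess which variables are independently associated with outcome". It gives no direction, no entry or removal threshold, and no order relative to the screen.

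The significance level comes from the diagnostic study's statistics, which section 2.2.2 takes over for basic analyses: "All testing will be two-tailed and P values less than 0.05 were considered to indicate statistical significance".

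On the candidates, section E says "We will evaluate 18 known predictors" and lists them. Section 2.2.2 repeats the list and adds "and copeptin levels in our multivariate analysis", which makes copeptin a nineteenth variable subject to the same screen. Neither section names a covariate that stays in the model whatever its P value.

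**The concern.** The protocol calls the 18 covariates known predictors, yet lets one sample decide which of them to adjust for. A weak but real confounder will often miss P<0.05 at this sample size. Once it is dropped, its effect passes into the coefficient of any retained variable correlated with it, copeptin included. The final P value and interval also take no account of the search that produced the model.

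The protocol itself gives reason to expect such correlations. The Introduction reports that ADH, which copeptin mirrors, correlated with stroke severity. Section C (Procedures) says that smoking can raise copeptin, and smoking history is among the 18 predictors.

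This analysis carries hypothesis 2 and is the basis of the sample size, and later intervention studies are to depend on the results. A false claim for copeptin and a missed real effect would both matter.

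**Working it through.** **The plan's own figures.** 18 × 10 = 180, 18 × 15 = 270 and 18 × 20 = 360, as in "a minimum sample size of 180 patients (for 10 observations per predictor) to 270 (for 15 observations per predictor" and the stated maximum. Expected analysable patients: 480 × 0.80 × 0.90 = 345.6, against a stated figure of about 350. Ischaemic stroke alone: 300 × 0.80 × 0.90 = 216. All reproduce. The protocol gives no error rate or effect size for copeptin's adjusted effect, so that part needs simulation.

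**Inputs from the protocol.** 18 covariates plus copeptin; a screen of all 19 at two-sided 0.05; N = 346 or 216.

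**Inputs assumed, not in the protocol.** 40% unfavourable outcome; one strong severity covariate (log OR 1.0 per SD); 0, 6 or 10 weak confounders; backward elimination at 0.05 after the screen. Copeptin's correlation with severity is 0 in (a), 0.5 in (b) and 0.4 in (c) to (f). There were 1000 runs per scenario, so the Monte Carlo standard error near 0.05 is √(0.05 × 0.95 / 1000) = 0.007.

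**No true copeptin effect: proportion of runs declaring copeptin significant**

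| Weak confounders | Full 19-variable model, N=216 / 346 | Screen + stepwise, N=216 / 346 |
|---|---|---|
| (a) none; copeptin unrelated to any covariate | 0.064 / 0.054 | 0.032 / 0.029 |
| (b) none; copeptin related to severity only | 0.054 / 0.060 | 0.024 / 0.049 |
| (c) six, log OR 0.15, r = +0.1 | 0.071 / 0.052 | 0.071 / 0.061 |
| (d) six, log OR 0.20, r = +0.2 | 0.050 / 0.060 | 0.179 / 0.222 |
| (e) ten, log OR 0.20, r = +0.2 | 0.075 / 0.052 | 0.482 / 0.590 |
| (f) six, log OR 0.20, r = −0.2 | 0.049 / 0.051 | 0.001 / 0.008 |

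In (d), each weak confounder passes the screen in only 20% (N=216) or 31% (N=346) of runs. As a rough check, bias ≈ sum of (log OR of each dropped confounder × its slope on copeptin given severity). That slope is 0.2 / (1 − 0.4²) = 0.238. At N=216 this gives 6 × 0.80 × 0.2 × 0.238 = 0.23, and at N=346 it gives 6 × 0.69 × 0.2 × 0.238 = 0.20. With copeptin kept in and the covariates screened, the simulated mean coefficients are 0.17 and 0.15. They are of the same order and somewhat smaller, because the formula ignores logistic attenuation and the fact that chance decides which confounders drop out.

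Exempting copeptin from the screen while still screening the covariates does not cure this: the error is 0.147 / 0.181 in (d) and 0.154 / 0.193 in (f).

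**True copeptin effect, log OR 0.3**

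- Confounding as in (d): the mean estimate when copeptin is selected is 0.604 (N=216) and 0.528 (N=346), against 0.334 and 0.325 in the full model.
- Six confounders at r = −0.2 and no correlation with severity: copeptin passes its own screen in 0.076 and 0.072 of runs. It is declared in 0.050 and 0.053, against 0.385 and 0.570 with the full model.

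**What a full model would cost.** At an assumed 30–50% unfavourable outcome, N=346 gives 104–173 events, or 5.5–9.1 per variable for 19 variables. N=216 gives 65–108 events, or 3.4–5.7 per variable.

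**What a short pre-specified set achieves.** A further simulation (500 runs) assumed severity log OR 1.0, age log OR 0.6, copeptin–severity r = 0.3, and eight weak confounders at log OR 0.2 and r = +0.2. Screening gave a false-positive rate of 0.24 (N=216) and 0.33 (N=346). A fixed set of severity, age and four of the eight gave 0.20 and 0.33; with only two of the eight it gave 0.37 and 0.57. Alternating the signs of the eight correlations brought the screened rate down to 0.016 and 0.044.

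**The case against.** The strongest reply is that the harm is conditional. Scenarios (a) to (c) show little or no inflation, and in (f) the rate falls below nominal. Inflation needs several weak confounders pushing the same way, and nothing in the protocol establishes that number or direction. Strong confounders are largely safe: at log OR 0.5 per SD, 81% (N=216) and 95% (N=346) pass the screen. This stands, and it rules out saying that the plan inflates copeptin's significance as a matter of course.

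The study is also declared exploratory, with later studies to follow. That lowers the severity. It does not make P values from a selected model support the protocol's stated aim.

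A reader might infer two further faults that the material does not support. One is that screening makes the model look better than it will perform. In a comparison at N=216, the full model had AUC 0.83 apparent and 0.74 in new patients, and the screened model 0.79 and 0.75; screening did not worsen the optimism. The other is that the sizing ignores the search. Section E multiplies by all 18 candidates, so the search over those 18 is counted.

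Bootstrap correction, calibration and penalisation are commonly left to a statistical analysis plan, which is not at hand. Their absence is no fault here. The screening and stepwise rules are different, because the protocol states them.

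**Conclusion.** The point holds in conditional form. The protocol fixes a data-driven selection rule, forces in no covariate and screens copeptin itself, so the resulting P values and estimates do not reliably support a statement of independent association.

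Under the assumed inputs, the false-positive rate for copeptin runs from below 5% to about 18–22% with six same-direction weak confounders and 48–59% with ten. With opposite confounding, a real effect can be almost entirely missed. The analysis output would not show which of these had happened.

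A reader might go further and call the prognostic analysis invalid. The documents do not support that: the size and direction of the error rest on confounder strengths and correlations that they do not give, and that stepwise follows the screen, backward at 0.05, is also assumed. This should be fixed, but it is not fatal to an exploratory study.

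**What to change.** Replace the screening sentences in sections 2.2.2 and E, and the stepwise sentence in section E, with the following:

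- An adjustment set chosen on clinical knowledge and fixed before the copeptin batch assay. It should hold at least age and NIHSS/GCS, plus as many of the 18 known predictors as the outcome events allow. Penalised estimation would let more of them stay.
- This set and copeptin remain in the model regardless of significance.
- Copeptin's added value is tested by comparing the model with and without it, and optimism-corrected performance is reported.
- Univariable results are descriptive only.
- The closing words of "Only variables significantly associated with the outcome will be assessed in a multivariate model performed separately for each parameter" are clarified: they could mean a model per outcome or a model per marker.

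No data collection changes, R is already named for analysis, and batch measurement after sample collection leaves time to lock the set. The cost is wider intervals. Residual confounding also remains if the set is cut short: as the check with four of eight weak confounders shows, a small core set alone does not restore a 5% error rate. It does remove the data-driven selection and the screening of copeptin.
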